**Secondary objectives:**

1. To determine the efficacy of povidone iodine in clearing COVID-19 virus located in the nasopharynx
2. To assess the adverse events among the groups

**METHODOLOGY**

**Study Design:** Open label randomized clinical trial.

**Place of Study:** Department of Otorhinolaryngology and Head Neck Surgery, in collaboration with Department of Virology and Department of Medicine, Dhaka Medical College Hospital, Dhaka, Bangladesh.

**Period of study:** The study period will be September 2020 to December 2020.

**Study population:** Confirmed cases of COVID-19 disease proven by RT-PCR testing.

**Sampling and statistical basis of the sample size:** The sample size was determined using the following formula:

**Sample size:**

- - For 80% power, Z_β_=.84
  - For 0.05 significance level, Z_α_=1.96
  - r=1 (equal number of cases and control)
  - σ=10.0
  - Difference = 5.0

Therefore, n=126

Including exclusion criteria total sample 63*2+

30*2=186.

Therefore, in each group, a total of 27 samples will be collected after randomization.

**Number of participants:** The total number of participants will be 27 in each arm (7 Arm x 27=a total of 189 sample).

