**Proposed Analysis Plan of the study:**

Data analysis will be performed by data management software, R-4.0.2’. Then, the principal investigator (PI) will also check and verify the data. Then data will be transferred to statistician. If it is consistent with the objectives, then the PI and his team will draft the final result.

The following procedure will be followed during data analysis. The RCT aims to determine whether povidone iodine can clear COVID-19 virus from the nasopharynx of COVID-19 positive patients. The analysis will be performed on an intention-to-treat basis and a per-protocol basis. Subgroup analyses based on the primary outcome will also be estimated. Although the study is not formally powered for these subgroup analyses, the analysis will be added to draw a more conclusive statement. Statistical significance is set at the 95% confidence level at the 5% acceptable error level. Differences will be considered significant at the P < 0.05 level for all these tests. The data will be expressed as the means ± standard deviations (SD) for continuous variables and as frequencies (%) for categorical variables. Chi-square test and Student’s t test or ANOVA will be used in cases of normally distributed data, and similar non parametric data will be used whenever appropriate. Data will be analyzed by SPSS 20 Windows version (Chicago, Illinois, USA), and graphs and charts will be expressed by Microsoft Excel 2016.

.

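### The 80% power is derived for two groups of 63, but the total is spread over seven arms of 27, so one PVP-I arm against its matching water arm has about 44% power

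*Protocol*

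**What the plan says.** The Protocol, under Sample size, lists the inputs "For 80% power, Z_β_=.84", "For 0.05 significance level, Z_α_=1.96", "r=1 (equal number of cases and control"), an SD of 10.0 and "Difference = 5.0". The result is "Therefore, n=126", which the next line breaks down as 63 times 2. An allowance of 30 times 2, attributed to exclusion criteria, raises this to 186.

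The section then concludes: "Therefore, in each group, a total of 27 samples will be collected after randomization". Under Number of participants it adds: "The total number of participants will be 27 in each arm (7 Arm x 27=a total of 189 sample").

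Procedure of randomization confirms seven equal arms: three PVP-I irrigation arms, two PVP-I spray arms, one distilled-water irrigation arm and one distilled-water spray arm. The Proposed Analysis Plan gives the aim as follows: "The RCT aims to determine whether povidone iodine can clear COVID-19 virus from the nasopharynx of COVID-19 positive patients". It lists chi-square, t test and ANOVA at P < 0.05. It does not say which arms are to be compared or pooled.

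**The concern.** The word for group changes meaning within the section. In the formula it is one of two groups, treated and control. In the conclusion it is one of seven arms. The 27 is presented as following from the 80% power calculation, but it comes only from dividing the inflated two-group total by seven.

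This matters because arm-level comparisons are part of what the trial is meant to deliver. The Conclusion in Part-A expects the study to show the optimal concentration, and that can only be learned by comparing arms. If a single concentration shows no significant difference from its control, a reader who trusts the 80% would take this as evidence against that concentration. In fact the 27 v 27 comparison would be more likely than not to miss the planned difference.

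There is a second gap. The SD of 10 and difference of 5 have no unit and are attached to no outcome, while the aim is phrased as clearing virus, assessed by repeat RT-PCR. The stated power therefore cannot be carried over to clearance.

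**Working it through.** **Inputs (Protocol, Sample size):** z = 1.96 (two-sided 0.05), z = 0.84 (80% power), SD 10, difference 5, ratio 1. The standardised difference is 5/10 = 0.5.

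**Step 1. Reproduce the plan's figure.**
n per group = 2 × (1.96 + 0.84)² × 10² / 5² = 2 × 7.84 × 100 / 25 = 62.7, so 63. Two groups give 126, which matches. Power at 63 v 63 is 80.1% (normal approximation) or 79.5% (t test).

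**Step 2. Trace the 27.**
126 + 60 = 186; 186 / 7 = 26.6, rounded up to 27; 7 × 27 = 189. The allowance of 60 is itself spread over the seven arms, so it does not restore the arm size to 63.

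**Step 3. Power for the planned 5-unit difference at the actual sizes.**
Noncentrality = 0.5 × √(n₁n₂/(n₁+n₂)); normal-approximation power = Φ(noncentrality − 1.96). For 27 v 27: 0.5 × √13.5 = 1.837, and Φ(−0.123) = 45.1%.

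| Contrast | n | Noncentrality | Power, normal | Power, t test |
|---|---|---|---|---|
| One PVP-I arm v its matching water arm | 27 v 27 | 1.837 | 45.1% | 43.8% |
| One PVP-I arm v both water arms | 27 v 54 | 2.121 | 56.4% | 55.4% |
| Spray PVP-I v spray water | 54 v 27 | 2.121 | 56.4% | 55.4% |
| Irrigation PVP-I v irrigation water | 81 v 27 | 2.250 | 61.4% | 60.6% |
| All PVP-I v all water | 135 v 54 | 3.105 | 87.4% | 87.1% |

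Of these, only the fully pooled contrast exceeds 80%. Irrigation PVP-I against both water arms (81 v 54) would just reach it (0.5 × √32.4 = 2.846; Φ(0.886) = 81%), but it sets one route against a mixture of two. None of these contrasts is specified in the Protocol.

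**Step 4. Difference detectable with 80% power at 27 v 27.**
2.8 × 10 × √(2/27) = 7.62 units by the normal approximation; 7.77 units by the t test. The plan assumes 5. Holding 80% for every pairwise comparison would need 7 × 63 = 441 patients, before any allowance or multiplicity adjustment.

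**Step 5. The same sizes on a clearance scale.**
The Protocol gives no clearance rate, so control clearance is assumed to lie between 2% and 30%. Fisher's exact test, two-sided 0.05:

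| n | Control v PVP-I | Difference (points) | Power |
|---|---|---|---|
| 27 v 27 | 2% v 32% | 30 | 79% |
| 27 v 27 | 20% v 60% | 40 | 80% |
| 27 v 27 | 30% v 72% | 42 | 81% |
| 54 v 135 | 2% v 15% | 13 | 83% |
| 54 v 135 | 30% v 54% | 24 | 83% |

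So 27 v 27 needs a difference of about 30 to 42 percentage points, and the pooled contrast about 13 to 24.

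**The case against.** The best defence is that the 80% was never claimed for single arms. The calculation speaks of two groups, and the Research Hypothesis and General Objective concern PVP-I nasal preparations as a whole. If the intended test is all PVP-I against all distilled water, 135 v 54 has about 87% power for the planned difference. This largely stands. A reader might infer that the trial is underpowered for its stated hypothesis, or that the sponsor believes each concentration has 80% power. The document supports neither. What remains is that the pooled contrast is nowhere specified, the calculation is not done for a 135:54 allocation, and 27 per arm is presented as a consequence of 80% power.

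Three other stronger readings also fail:

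- **Every arm-level comparison has 44% power.** That figure is for one arm against one control arm. Against both control arms it is about 55%.
- **The equal ratio misdescribes the design.** At 27 v 27 the ratio is 1, and the arms are equal by design. It misfits only pooled contrasts such as 135 v 54. At arm level the fault is the number, not the ratio.
- **The extra 60 will be lost to attrition, lowering power further.** The Protocol ties them to exclusion criteria and counts the 27 after randomization. It takes the repeat sample within 15 minutes of the intervention and replaces patients who withdraw before any study procedure. It gives no basis for losing a third of those randomized.

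It is also fair to say that the outcome scale is not fixed. The wording points to clearance, but the Rationale mentions titres and the analysis plan lists tests for means beside chi-square. The sound criticism is that the SD and difference belong to no named outcome, not that a mean is certainly the wrong scale. A separate statistical plan may define the contrast, but the sample size justification is given here and does not support the arm size it concludes with.

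**Conclusion.** The point holds at arm level. The 80% power belongs to 63 v 63, and the seven-arm design offers no comparison of that size between single arms. For the planned 5-unit difference, power is about 44% for one PVP-I arm against its matching water arm and about 55% against both water arms; 80% at 27 v 27 would need about 7.6 to 7.8 units. The fully pooled contrast has about 87%, so the trial can be adequately sized for the general hypothesis if that is the intended test.

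The power figures for means take the Protocol's SD and difference at face value, at two-sided 0.05 without multiplicity adjustment. The clearance figures depend on the assumed control clearance of 2% to 30%. Power for the outcome actually sought cannot be derived from the document.

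**What to change.** Keep 189 patients and restate the justification:

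1. Remove the implication that 27 per arm follows from 80% power.
2. State which comparison the power refers to and on which outcome. All PVP-I (n = 135) against all distilled water (n = 54) fits the Research Hypothesis and is one suitable choice, though not the only one.
3. Give the power or detectable difference for that outcome at the actual group sizes. If the outcome is the proportion RT-PCR negative, state the assumed control clearance.
4. State that the 27-per-arm comparisons are secondary and fall well short of 80% power for the planned effect. Give their detectable difference on the clearance scale: about 30 to 42 percentage points for 27 v 27 if control clearance is 2% to 30%. Do not simply write in 44%, since that figure rests on a 5-unit difference with no named outcome.

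This is a change of wording only and needs no extra patients. The downside is that the stated power for comparing concentrations becomes openly less favourable.

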**Procedure of randomization:** The study participants will be randomly assigned in this study into seven (7) equal Arm, where each arm has equal opportunity to receive any treatment option. Randomization will be performed by computer generated random sequences.

- - Arm 1 will receive povidone iodine (PVP-I) nasal irrigation at a concentration of 0.4%
  - Arm 2 will receive povidone iodine (PVP-I) nasal irrigation at a concentration of 0.5%
  - Arm 3 will receive povidone iodine (PVP-I) nasal irrigation at a concentration of 0.6%
  - Arm 4 will receive PVP-I nasal spray at a concentration of 0.5% with standard care.
  - Arm 5 will receive PVP-I nasal spray at a concentration of 0.6%
  - Arm 6 (placebo comparator group) will receive nasal irrigation with distilled water
  - Arm 7 (placebo comparator group) will receive nasal spray with distilled water

This can be done quickly, with baseline information typically captured in <15 min. Recruitment & randomization will be performed contemporaneously with assessment/resuscitation of patients by a second person so that medical care is not delayed by recruitment. Patients will only be randomized once baseline data have been entered; after this has been done, participants will not be withdrawn from the study. Following tossing, the trial physicians reported the principal investigator (PI) of the trial, and then the PI handed over an opaque sealed envelope, which will be numbered sequentially to correspond to patient enrolment numbers, which will be used for concealment of treatment allocations. Envelopes will be kept in a locked drawer and will be opened in strict numerical order by supervisor in the presence of the nursing supervisor of the study unit. Allocation between arms will initially be equal, although this may be revised following guidance of the PI and his team (as per the statistical plan).

**Withdrawal of study participants:** Participants are free to withdraw from the study at any point, for any reason. If this occurs, the primary reason for withdrawal will be documented in the participant’s case record form. The participant will have the option of withdrawal from:

- Study medication with continued study procedures and collection of clinical and safety data,
- All aspects of the trial but continued use of data collected up to that point,
- All aspects of the trial with the removal of all previously collected data, or

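### A two-group sample size is divided among seven arms, so on the protocol's own inputs one arm against its own water arm has about 44% power, not 80%

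*Protocol*

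**What the plan says.** The Sample size section of the protocol lists its inputs as "For 80% power, Z_β_=.84", "For 0.05 significance level, Z_α_=1.96", "r=1 (equal number of cases and control"), an SD of 10.0 and "Difference = 5.0". From these it states "Therefore, n=126". It then adds an allowance, "Including exclusion criteria total sample 63*2" plus 30*2, which gives 186. The next sentence is "Therefore, in each group, a total of 27 samples will be collected after randomization", and the section ends with seven arms of 27, a total of 189.

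The Procedure of randomization section confirms the design: "The study participants will be randomly assigned in this study into seven (7) equal Arm". Five arms receive povidone-iodine (three irrigation concentrations and two spray concentrations). Two receive distilled water, one by irrigation and one by spray.

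The analysis plan lists chi-square, t test or ANOVA at P < 0.05. Nowhere does the protocol say that arms will be pooled for the main comparison, and nowhere does it recalculate power for 27 per arm.

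**The concern.** The formula gives the number needed in each of two groups. The protocol treats the resulting total as a pool of patients to be shared among seven arms, and presents the share as if it still followed from the 80% power calculation. Each arm gets 27 where the calculation asks for 63 in each compared group, or 43% of the requirement (27/63).

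This matters because of what the design is for. The summary's conclusion expects the trial to identify an optimal concentration. Testing three irrigation strengths and two spray strengths, with a water arm for each route, serves comparisons at arm or route level. If those comparisons are believed to have 80% power, a non-significant result for one concentration can be taken as evidence that it does not work. On the stated inputs, such a comparison would miss the planned difference more often than it would detect it.

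**Working it through.** **Inputs, all from the Sample size section:** difference 5.0, SD 10.0 (standardised difference 0.5), Z = 1.96 (so two-sided 0.05), Z = 0.84 (80% power), r = 1. Number and type of arms come from Procedure of randomization.

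**Step 1. Reproduce the protocol's figure.**

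n per group = 2 × SD² × (1.96 + 0.84)² / difference² = 2 × 100 × 7.84 / 25 = 62.72, rounded up to 63.

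Two groups: 63 × 2 = 126, as stated. A one-sided test would give 50 per group, so the calculation is two-sided. With the allowance: 126 + 60 = 186, or 93 per group.

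**Step 2. Find where 27 comes from.**

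186 / 7 = 26.57, rounded up to 27; 27 × 7 = 189. No other use of the stated inputs leads to 27.

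**Step 3. Power at the sizes actually planned.**

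For groups of n1 and n2, the standard error is 10 × √(1/n1 + 1/n2). The noncentrality is 5 divided by that standard error. Power is taken from the noncentral t distribution with n1 + n2 − 2 degrees of freedom. The last column is the normal approximation, which is the protocol's own method.

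| Contrast | n1 v n2 | SE | 5/SE | Power, t test | Power, normal |
|---|---|---|---|---|---|
| As calculated | 63 v 63 | 1.78 | 2.81 | 79.5% | 80.1% |
| One arm v its own water arm | 27 v 27 | 2.72 | 1.84 | 43.8% | 45.1% |
| One arm v both water arms | 27 v 54 | 2.36 | 2.12 | 55.4% | 56.4% |
| Both spray arms v spray water | 54 v 27 | 2.36 | 2.12 | 55.4% | 56.4% |
| Three irrigation arms v irrigation water | 81 v 27 | 2.22 | 2.25 | 60.6% | 61.4% |
| All povidone-iodine v all water | 135 v 54 | 1.61 | 3.11 | 87.1% | 87.4% |

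**Step 4. Difference detectable with 80% power at 27 v 27.**

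2.8 × 10 × √(2/27) = 7.6 by the protocol's formula (7.8 by t test), against a planned 5.0.

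**Step 5. What 80% per arm would require.**

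63 in every arm: 7 × 63 = 441 before any allowance, or 7 × 93 = 651 with the protocol's own 30 extra per group. Neither figure adjusts for multiple comparisons. With a Bonferroni correction for five comparisons (0.05/5 = 0.01), power at 27 v 27 is 23% by the normal approximation.

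**The case against.** The best defence is that the 80% was never meant for single arms. The hypotheses, the general objective and the stated aim of the analysis all refer to povidone-iodine as a class, and the sample-size inputs speak of cases and controls. On that reading the contrast is 135 v 54, with 87% power. This part stands: it is the contrast closest to the written hypothesis, and it is adequately powered on the stated inputs if all 189 are evaluable. It does not rescue the text. No pooling is specified, r = 1 does not describe 135 v 54, and 27 is presented as the required size of each group. An optimal concentration cannot be read from a pooled contrast.

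A second objection is that the difference and SD are attached to no named outcome, while the efficacy measurement is a repeat RT-PCR and the aim is clearance. If clearance is compared as a proportion, 27 v 27 may or may not be enough. With assumed clearance rates and an uncorrected chi-square test, power is 49% for 10% v 30%, 77% for 10% v 40% and 93% for 10% v 50%. This is fair. The 44% follows from the protocol's own inputs and is not an estimate of the trial's power for clearance. The division by seven is an error either way, because a per-group requirement is not met by sharing the two-group total among more groups.

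Third, one might ask what happens if the 60 added patients are all lost: 126/7 = 18 per arm, 31% power for one arm against its water arm. The protocol links the 60 to exclusion criteria and counts the 27 after randomisation, and the repeat sample is taken within minutes, so losses on that scale are not to be expected. The conclusion does not rely on this case.

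**Conclusion.** The point holds. The calculation for two groups is correct (63 per group, 126 in all), but the step from there to 27 per arm is invalid. On the protocol's own inputs, with all 27 per arm evaluable and no multiplicity adjustment, power is about 44% for one arm against its own water arm, 55% for spray, 61% for irrigation and 87% for all povidone-iodine against all water. The stated 80% is therefore wrong for every contrast at arm or route level and is reached only by a pooled contrast that the protocol does not define. These percentages assume a continuous outcome with SD 10.0 and a difference of 5.0. The protocol names no such outcome.

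**What to change.** Keep 189 patients and correct the Sample size section:

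1. Remove the inference that 27 per group follows from the 80% calculation, and say that 63 per group refers to a comparison of two groups.
2. Name the outcome and unit to which the difference of 5.0 and SD of 10.0 belong. If the outcome is clearance, replace them with assumed clearance proportions and recompute.
3. State the power of each planned contrast at the sizes actually used. On the present inputs this is about 44% (arm v own water arm), 55% (spray), 61% (irrigation) and 87% (all povidone-iodine v all water, 135 v 54, all evaluable).
4. Specify the pooled contrast as the one carrying the power claim, and label arm-level and route-level comparisons as estimation or exploratory, so that a non-significant arm is not read as showing no effect.

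The cost is protocol wording and no extra patients. The price is a less favourable power statement for individual concentrations. Keeping 80% for each arm instead would take 441 patients before any allowance.

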**Inclusion criteria:**

- - - - Age: 15-90 years
      - Either gender
      - Patients diagnosed with COVID-19 disease by RT-PCR
      - Have confirmed COVID-19 symptoms and symptom onset within the past 4 days
      - Capable of using a nasal spray device and perform nasal irrigation required by the study
      - Willing to participate

**Exclusion criteria:**

- Patients with known sensitivity to PVP-I aqueous antiseptic solution or any of its listed excipients
- Previously diagnosed thyroid disease
- Patients with chronic renal failure: stage ≥3 by estimated glomerular filtration rate (eGFR) Modification of Diet in Renal Disease (MDRD)
- Patients with acute renal failure (KDIGO ≥stage 2: creatinine ≥2 X baseline)
- Pregnant and lactating mother
- Current requirement for invasive or noninvasive ventilation or planned within the next 6 hours.

**Operational definitions:**

**Povidone Iodine (Kirk-Bayley *et al.*, 2020):**

Povidone-iodine (iodine with the water-soluble polymer polyvinylpyrrolidone, PVP-I) was discovered in 1955 at the Industrial Toxicology Laboratories in Philadelphia by H. A. Shelanski and M. V. Shelanski. It was developed in order to find an antimicrobial iodine complex that was less toxic than tincture of iodine, which caused burn. PVP-I antibacterial activity is enhanced by dilution of the usually available 10% w/w cutaneous solution, from 1:2 dilution up to a 1:100 dilution (0·1%).

**Method and data collection:**

**Participant selection and enrolment:** All patients admitted to the medical wards through the emergency department or outpatient department with suspected COVID-19 cases will be initially approached and screened for confirmation of COVID-19. Confirmation of COVID-19 will be performed by positive impression of RT-PCR results. Following confirmation of the viral infection, the patients will be seen by the ward doctors and clinical trial physicians (registered physicians). Moreover, baseline complete blood count (CBC) will be performed for each patient. Chest X-ray/high-resolution computed tomography (HRCT) will be performed in necessary cases. The ward doctors and trial physicians will together care for the patient; then, the patients will be briefed about the aim, objective and details of the procedure of the study. If without capacity, their relatives will be approached about the trial and seek their consent for recruitment. As this study will be confined to a tertiary care hospital, patients will be recruited up to day 4 of illness.

**Consenting participants:** It will be prioritized that the patients will be treated early for COVID-19 management by a standard regimen and in accordance with the guidance of the national guidelines. Within the shortest possible time, preferably within 4 hours of admission, the consenting procedure will be completed either from the patient or from the attendant/legal guardian of the patients to obtain the full potential benefit of the treatment. Written informed consent will be obtained from the patient in their own language [Bengali] by trial physicians working on the trial.

**Screening for eligibility:** During admission, demographic and clinical details, including name, age/date of birth, sex, duration of onset of fever and hospitalization, vital statistics will be recorded before randomization. RT-PCR for COVID-19 will be used for confirmation of COVID-19 virus infection. A screening log will be maintained including these essential details and the decision made by the patient, attendant or legal guardian where appropriate concerning recruitment. Ineligible and non-recruited patients will also be cared for by ward physicians following standard treatment guidelines.

**Procedure of randomization:** The study participants will be randomly assigned in this study into seven (7) equal Arm, where each arm has equal opportunity to receive any treatment option. Randomization will be performed by computer generated random sequences.

- - Arm 1 will receive povidone iodine (PVP-I) nasal irrigation at a concentration of 0.4%
  - Arm 2 will receive povidone iodine (PVP-I) nasal irrigation at a concentration of 0.5%
  - Arm 3 will receive povidone iodine (PVP-I) nasal irrigation at a concentration of 0.6%
  - Arm 4 will receive PVP-I nasal spray at a concentration of 0.5% with standard care.
  - Arm 5 will receive PVP-I nasal spray at a concentration of 0.6%
  - Arm 6 (placebo comparator group) will receive nasal irrigation with distilled water
  - Arm 7 (placebo comparator group) will receive nasal spray with distilled water

This can be done quickly, with baseline information typically captured in <15 min. Recruitment & randomization will be performed contemporaneously with assessment/resuscitation of patients by a second person so that medical care is not delayed by recruitment. Patients will only be randomized once baseline data have been entered; after this has been done, participants will not be withdrawn from the study. Following tossing, the trial physicians reported the principal investigator (PI) of the trial, and then the PI handed over an opaque sealed envelope, which will be numbered sequentially to correspond to patient enrolment numbers, which will be used for concealment of treatment allocations. Envelopes will be kept in a locked drawer and will be opened in strict numerical order by supervisor in the presence of the nursing supervisor of the study unit. Allocation between arms will initially be equal, although this may be revised following guidance of the PI and his team (as per the statistical plan).

**Withdrawal of study participants:** Participants are free to withdraw from the study at any point, for any reason. If this occurs, the primary reason for withdrawal will be documented in the participant’s case record form. The participant will have the option of withdrawal from:

- Study medication with continued study procedures and collection of clinical and safety data,
- All aspects of the trial but continued use of data collected up to that point,
- All aspects of the trial with the removal of all previously collected data, or
- All aspects of the trial with the removal of previously collected data and stored participant samples.

Randomized patients who wish to withdraw from the study before they have undertaken any study-related procedures will be replaced. Data on the original participant will be kept on the CRF/database if the participant agrees to this.

